Among subjects, 500 patients will be selected to conduct pharmacometabolomics analysis compared with 500 healthy volunteers for detecting disease-associated metabolites. After the evaluation of patients’ curative parameters (listed below), preliminary pharmacogenomics and pharmacometabolomics analysis will be carried out. We will pick up 500 patients, half of them have good response from significant effective group and half have no response from deterioration group, their blood samples will be analyzed by pharmacogenomics and pharmacometabolomics to find out response-associated predictors, and then the predictors of patients’ response to Conbercept will be further validated in all of the recruited subjects. Figure 1 is the study design flow.

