### Main outcome measures

#### Primary outcome

The primary outcome is visual changes primarily recorded as best-corrected visual acuity (BCVA) in EDTRS letters at V2, V3, V4, and V5 minus baseline vision (V1). The efficacy was graded as significantly effective (visual improvement ≥15 letters in EDTRS); effective (visual improvement ≥5 letters and < 15 letters in EDTRS); invalid (visual improvement < 5 letters and visual reduction< 5 letters in EDTRS); deterioration (visual reduction≥5 letters in EDTRS) [15]. Moreover, patients graded as significantly effective and effective that is BCVA improvement≥5 letters in EDTRS are defined as having response to Conbercept treatment and the response rate (the rate of patients graded as significantly effective and effective) will be assessed in the whole study population and in each diseases.

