#### Secondary outcome

The changes of retinal edema will be evaluated by central fovea retinal thickness (CRT in μm) at V2, V3, V4 and V5.The different therapeutic regimens of Conbercept prescribed by doctors and applied on different diseases in real-world clinical practice will be assessed, including number of treatments, frequency of injection (times per year), interval time (months).Response-related factors for Conbercept to macular neovascular diseases after 3 months’ treatment will be examined. We will compare the macular leakage area (mm^2^) and the CNV area (mm^2^) to baseline in FFA between patients who response to Conbercept treatment and patients with no response, and their relationship with the responders and nonreponders will be further analyzed.The potential biomarker of patients’ response to Conbercept will be investigated by pharmacogenomics and pharmacometabolomics as mentioned above in study design. The genomic variation between patients who respond to Conbercept treatment and patients who have no response to Conbercept drug treatment will be detected. Conbercept-sensitive associated Single Nucleotide Variations (SNVs) will be picked out by comparing the data of single nucleotide polymorphisms dbSNP and hapMap Database to remove common single nucleotide polymorphisms (SNPs) or SNVs information. Then we will design gene panel based on Next Generation Sequencing to validate the Conbercept-sensitive genomic regions among the whole study population. Besides, prediction model will establish to figure out Conbercept-sensitive genotype in macular neovascular diseases. For pharmacometabolomics studies, blood samples of patients and healthy volunteers will be analyzed by mass spectrometry to primarily screen disease-associated metabolites. The associations of genotype and metabolites with clinical endpoint will be assessed and further validated in the whole study population. Those signatures (gene/ metabolites) will be considered to be predictors of patients who will possibly have good response to Conbercept treatment, and those in non-responders will be recognized as potential predictors of patients who do not respond to Conbercept. Finally, we will build an Oracle database about macular neovascular diseases based on clinical information, pharmacogenomics, and pharmacometabolomics.Safety data: adverse events (AE) and severe adverse events (SAE) were defined according to other large-scale clinical trial on intravitreal injection of anti-VEGF drugs [14–16]. AE and SAE need to be recorded, and their relevance to drug or procedures will be estimated. The number and percentage of AE and SAE in the whole study population and in each disease will be calculated.

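### Predictors are discovered by comparing gains of 15 or more letters with losses of 5 or more, but are labelled as predictors of response and non-response; the planned validation would not show the difference.

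*Protocol article*

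**What the plan says.** The *Primary outcome* section of the protocol article grades change in best-corrected visual acuity in four steps. The top grade is "significantly effective (visual improvement ≥15 letters in EDTRS"). Next comes the effective grade, a gain of 5 to 14 letters. The third is "invalid (visual improvement < 5 letters and visual reduction< 5 letters in EDTRS"), and the last is "deterioration (visual reduction≥5 letters in EDTRS"). The section then draws one line through the four grades: "BCVA improvement≥5 letters in EDTRS are defined as having response to Conbercept treatment". Non-response is not defined separately. As the complement of response, it is the invalid grade plus the deterioration grade.

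The *Study design and objectives* section sets up discovery: "We will pick up 500 patients", of whom "half of them have good response from significant effective group and half have no response from deterioration group". That implies 250 against 250. The predictors found "will be further validated in all of the recruited subjects".

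The *Secondary outcome* section refers back to this design, describes it as a comparison of patients who respond with patients who do not, and states how the signatures will be labelled: "those in non-responders will be recognized as potential predictors of patients who do not respond to Conbercept".

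**The concern.** A patient with no change in letters is a non-responder under the primary outcome but cannot enter the no-response half of the discovery sample. A patient who gains 8 letters is a responder but cannot enter the good-response half. Discovery therefore answers a narrower question than its labels suggest: which markers distinguish large gains from losses.

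The article's motive, in its *Background*, is that some patients respond poorly or not at all to an expensive drug. Patients whose vision does not change fit that description directly. Markers specific to them are out of reach of the discovery step, and a marker of vision loss may be presented as telling the clinician something about them. A later reader would see a validated predictor of non-response and could not tell which patients it describes.

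**Working it through.** **1. The definitions side by side**

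| Change in letters | Grade | Primary outcome | Discovery sample |
|---|---|---|---|
| gain of 15 or more | significantly effective | responder | good response, 250 |
| gain of 5 to 14 | effective | responder | not sampled |
| within 5 either way | invalid | non-responder | not sampled |
| loss of 5 or more | deterioration | non-responder | no response, 250 |

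The two discovery groups are subsets of responders and non-responders. The gap is on both sides.

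**2. How many patients are left out**

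The article gives no distribution of change for this cohort and no figure of its own to reproduce. Assumptions: change is normal with mean μ of 3 to 9 letters and SD σ of 12 to 18. The upper mean is close to the 8.97 letters that *Background* quotes for one dose group after three months. Whole letters are handled with cuts at ±4.5 and 14.5.

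- Deterioration = Φ((−4.5 − μ)/σ)
- Invalid = Φ((4.5 − μ)/σ) − Φ((−4.5 − μ)/σ)

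μ = 9, σ = 12: deterioration Φ(−1.125) = 13.0%; invalid 35.4% − 13.0% = 22.4%. Invalid share of non-responders = 22.4/35.4 = 63%.

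μ = 3, σ = 18: deterioration Φ(−0.417) = 33.8%; invalid 53.3% − 33.8% = 19.5%. Share = 19.5/53.3 = 37%.

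The other combinations lie between. On the responder side, the unsampled effective grade at μ = 9 is 32.3/64.6 = 50% of responders (σ = 12) and 21.9/59.9 = 37% (σ = 18).

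**3. Would whole-cohort validation catch a deterioration-only marker?**

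Take a marker carried by 20% of all patients, the invalid grade included, but by 40% of deteriorated patients. Test at two-sided p < 0.05, the cutoff in *Data analysis*, with power = Φ((d − 1.96·SE₀)/SE₁).

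Discovery, 250 v 250: d = 0.20; SE₀ = √(0.3 × 0.7 × 2/250) = 0.0410; SE₁ = √((0.24 + 0.16)/250) = 0.0400. Power = Φ(2.99) = 0.999; odds ratio 2.67.

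Validation assumes 5,000 × 0.8 = 4,000 evaluable patients, from the enrolment target and the 20% limit on loss to follow-up, split at the 5-letter gain. The least favourable case is μ = 9, σ = 12:

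- Non-responders 1,415, responders 2,585.
- Prevalence in non-responders = 0.2 + 0.2 × 13.0/35.4 = 0.274.
- d = 0.0736, SE₀ = 0.0138, SE₁ = 0.0142; power = Φ(3.27) = 0.999.
- Odds ratio = (0.274/0.726)/(0.2/0.8) = 1.51.

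At μ = 3, σ = 18 the prevalence is 0.327, the odds ratio 1.94 and the power above 0.999.

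With a weaker marker (30% in deteriorated patients), discovery power is 0.73 and validation power 0.77 to above 0.99, with odds ratios of 1.24 to 1.43.

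**4. What catches it**

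Leaving out the 500 is not enough. At μ = 9, σ = 12 there remain 521 − 250 = 271 deteriorated, 894 invalid and 2,335 responders. Pooled prevalence in non-responders is (894 × 0.2 + 271 × 0.4)/1,165 = 0.247, and power for the 40% marker is still 0.88. Comparing the invalid grade alone with responders is 20% v 20%, which reaches p < 0.05 only 5% of the time. That contrast is also well sized: a marker truly carried by 30% of the invalid grade would be found with power above 0.99, and one carried by 25% with power 0.87.

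**The case against.** A reader might infer that the article holds two conflicting definitions of non-response, or that markers of deterioration will inevitably be reported as markers of non-response. The text supports neither. Every deteriorated patient is a non-responder under the primary outcome, and every patient gaining 15 letters is a responder. Sampling the extremes is an accepted way to gain discovery power. The article calls its initial omics analysis preliminary, speaks of potential predictors, and plans validation in the whole study population, which contains the invalid grade. *Data analysis* also evaluates prediction models by discrimination, calibration and decision curves, so a p-value is not the only test.

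A reader might also argue that the no-response half should be redrawn to include stable patients. That costs discovery power, would leave the matching gap among responders, and could blur the contrast. Nothing in the article settles whether stable vision on treatment is failure or disease control.

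The marker in the check is also a deliberately clean case, with no enrichment at all in the invalid grade. Even so, it is associated with non-response as the primary outcome defines it, only more weakly.

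All of this stands against the stronger readings. What remains is the label. The article never describes the two groups as a sampling device, and it carries the signatures over to non-responders in general. The planned validation does not protect that label: it reuses the discovery patients, and nothing in it keeps the two non-responder grades apart.

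**Conclusion.** The point holds as one of labelling and validation, not as a fault in the extreme-group sampling. About 37-63% of non-responders contribute nothing to discovery, and a marker of deterioration alone is liable to be confirmed as a marker of non-response.

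The share rests on the assumed normal distribution, mean and SD; it measures who is unsampled, not how often a marker would be mislabelled. The power figures rest on the assumed marker prevalences, on 4,000 evaluable patients, and on validation against the pooled 5-letter split, which is the only response definition the article gives. A stricter threshold would lower the powers but would not separate the two grades. The mismatch between label and sample is exact and needs no assumption.

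**What to change.** Keep the extreme-group discovery sample, with three changes:

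1. In *Study design and objectives* and *Secondary outcome*, name the contrast as *15 or more letters gained v 5 or more letters lost*, in place of good response v no response.
2. Validate against the primary-outcome definition in patients outside the discovery 500, and report invalid v responders and deterioration v responders separately.
3. Call a signature a predictor of non-response only if it also separates the invalid grade from responders. Otherwise report it as a predictor of deterioration.

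The cost is one further contrast on data already being collected, a validation set smaller by 500 (3,500 of an assumed 4,000), and a narrower claim for some markers. Removing 250 patients from each extreme also thins those grades: at mean 9 and SD 12, deterioration falls from 13.0% to 271/3,500 = 7.7%. Calibration in the remaining patients should be read with that in mind. No new patients, visits or samples are needed. *Participants and recruitment* reports that the first pharmacogenomic analysis is already under way, so the wording should be settled soon.

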For Pharmacogenomics and pharmacometabolomics, two kinds of statistical analysis will be implemented: 1) multivariate statistical analysis such as random forest, support vector machine learning, principal component analysis (PCA), partial least square discriminant analysis (PLS-DA), orthogonal partial least square discriminant analysis (OPLS-DA). 2) univariate statistical analysis, correlation analysis, and the regression analysis will be used. The predictor-ranking model will be determined by significant cutoff values (*p* < 0.05). All of data will be analyzed by R language (http://cran.r-project.org/) or SPSS (version 19.0) or SAS (University Edition) software.

To enhance comparability between outcome measures, we will select some comparable subgroups for analysis. Subgroups analysis includes comparison between healthy controls (from Ophthalmic Bio-bank of Shanghai Jiaotong University) and AMD patients, PCV patients, and CNV secondary to PM patients respectively for detecting the disease biomarkers; comparison between AMD, PCV and CNV secondary to PM patients to analyze the different signatures within different macular neovascular diseases; comparision between patients who have good response and who have no response to Conbercept in AMD patients, PCV patients, CNV secondary to PM patients respectively to explore the potential predictors of patients’ response to Conbercept treatment.

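### The omics discovery groups are picked on raw BCVA change, without matching or named adjustment for baseline BCVA and without a stated classifying visit, so markers of starting vision may be read as markers of response

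*Protocol article*

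**What the plan says.** All references are to the Protocol article.

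- **Selection.** *Study design and objectives* takes 500 patients, "half of them have good response from significant effective group and half have no response from deterioration group". The time of this step is given only as: "After the evaluation of patients’ curative parameters (listed below), preliminary pharmacogenomics and pharmacometabolomics analysis will be carried out". Predictors found there are then to be validated in all recruited subjects.
- **Grades.** *Primary outcome* defines the measure as "best-corrected visual acuity (BCVA) in EDTRS letters at V2, V3, V4, and V5 minus baseline vision (V1"). The upper group is "significantly effective (visual improvement ≥15 letters in EDTRS") and the lower is "deterioration (visual reduction≥5 letters in EDTRS"). A grade therefore exists at each of four visits.
- **Response.** The same section states that "patients graded as significantly effective and effective that is BCVA improvement≥5 letters in EDTRS are defined as having response".
- **Time point.** *Secondary outcome* has an item that begins "Response-related factors for Conbercept to macular neovascular diseases after 3 months". The separate biomarker item gives no visit and refers back to the study design section.
- **Analysis.** *Data analysis* allows multivariable models, and propensity score matching or inverse probability weighting where these do not suffice. Baseline BCVA is not named. For the omics data it lists multivariate classifiers and says that "univariate statistical analysis, correlation analysis, and the regression analysis will be used", with a cut-off of p < 0.05. It also plans the comparison of good response with no response separately within AMD, PCV and CNV secondary to PM.

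**The concern.** Change is follow-up minus baseline, so baseline enters it with a negative sign. Measurement error in the baseline reading is enough to push the correlation between change and baseline below zero. Taking the two tails of change then magnifies any difference in starting vision between the groups.

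A gene variant or metabolite that goes with poor starting vision (through severity or age, for example) can then separate the groups without saying anything about response beyond what the V1 chart reading already tells the clinician. Validation in the whole cohort does not screen out such a marker if it uses the same unadjusted change, because the same correlation operates there.

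The open visit adds a second weakness. A patient may be in the upper group at one visit and not at another, so membership depends on a choice that the shown text does not fix. The Discussion expects these predictors to guide individual treatment.

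**Working it through.** **What can be reproduced.** The article gives no power calculation, effect size or SD for the omics set. The only figure is 500/2 = 250 per group. The rest is illustration.

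**Inputs from the article:** cut-offs of +15 and −5 letters; 250 per group; p < 0.05 (taken as two-sided); more than 5000 patients with loss to follow-up below 20%, so about 5000 × 0.80 = 4000 evaluable; a mean 3-month change of 8.97 letters in one arm of the earlier trial cited in *Background*, used only as an alternative centre.

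**Assumptions not in the article:** change normal with mean 7 and SD 14 letters (varied below); baseline SD 18 letters; correlation r of change with baseline from 0 to −0.4; marker correlated 0.2 with baseline and linked to change only through baseline.

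**Step 1: distance between the tails.** With φ the standard normal density:
- Upper: z = (15 − 7)/14 = 0.571; tail probability 0.284; mean of the tail φ(z)/0.284 = 0.3388/0.2839 = 1.19 SD.
- Lower: z = (−5 − 7)/14 = −0.857; tail probability 0.196; mean of the tail −0.2763/0.1957 = −1.41 SD.
- Distance: 1.194 + 1.412 = 2.606 SD of change.

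**Step 2: baseline gap and false positives.** Baseline gap = |r| × 2.606. Marker shift = 0.2 × gap. Standard error of the difference ≈ √(2/250) = 0.0894. λ = shift/0.0894. Rejection rate = Φ(λ − 1.96) + Φ(−λ − 1.96).

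| r | Baseline gap (SD) | Letters at SD 18 | λ | Rejection at 0.05 |
|---|---|---|---|---|
| 0 | 0 | 0 | 0 | 5% |
| −0.1 | 0.26 | 4.7 | 0.58 | 9% |
| −0.2 | 0.52 | 9.4 | 1.17 | 21% |
| −0.3 | 0.78 | 14.1 | 1.75 | 42% |
| −0.4 | 1.04 | 18.8 | 2.33 | 64% |

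Simulations with 600 to 1000 draws, centred at 7 or 8.97 letters, scatter around these values: 9%, 20–25%, 38–43% and 60–68%. With mean change 8.97 and SD 12 to 18, the gaps are 0.24–0.28, 0.47–0.56, 0.71–0.84 and 0.95–1.12 SD. With marker–baseline correlations of 0.1 to 0.3 (mean 8.97, SD 15), the rejection rate runs over 7–40%, 13–74% and 21–93% at r = −0.2, −0.3 and −0.4.

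**Step 3: is a negative r plausible?** The follow-up variance is 18² + 14² + 2r × 18 × 14 = 520 + 504r. At r = 0 the follow-up SD would have to be √520 = 22.8 letters, against 18 at baseline. At r = −0.4 it is √318.4 = 17.8, about unchanged. So r = 0 requires the spread of vision to widen clearly under treatment.

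**Step 4: does adjustment work?** With baseline as a covariate, the simulated rejection rate was 4–7% in every scenario, which is nominal within simulation error. This holds for a marker linked to change through the recorded baseline; error in that reading would leave some residual.

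**Step 5: visit.** With mean 8.97, SD 15 and a between-visit correlation of 0.5 to 0.8 (assumed), 56–73% of patients graded as gaining at least 15 letters at one visit keep that grade at another. For deterioration it is 41–63%.

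**Step 6: room to match.** Of 4000 evaluable patients, mean 8.97 with SD 12 to 18 gives 1230–1475 gainers and 488–875 losers, against 250 needed from each.

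**The case against.** The strongest reply is that the article is a condensed protocol. *Data analysis* opens in terms that cover all data and provides for multivariable models and weighting; which covariates enter is detail for the full protocol or analysis plan, neither of which is shown. Extremes for discovery followed by validation in the full cohort is a legitimate two-stage design. The 3-month item stands in the same outcome list as the biomarker item, and the flowchart, which is not shown, may mark the classifying visit.

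Much of this stands. It would be wrong to say that the plan has no confounder control, and the visit is a request for clarification. The absence of a covariate list alone would be no finding. What remains is the selection rule that the article does state: two tails of raw change with no reference to baseline. Generic adjustment does not commit the omics models to baseline BCVA, and validation on unadjusted change repeats the problem.

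Three stronger readings are tempting but unsupported:
- **Confounding by disease mix.** The comparison of good response with no response is planned within each disease. Only the numbers per disease in the pick are left uncontrolled.
- **Two conflicting meanings of no response.** Patients who lose at least 5 letters are a subset of those who do not gain at least 5. Sampling from the subset does not redefine the whole.
- **Discrimination from the extremes reported as cohort performance.** No section says this. AUC and calibration are attached to models that predict response, and validation is in all subjects.

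**Conclusion.** The point holds in a limited form. The discovery groups are chosen on the extremes of raw BCVA change, baseline BCVA is neither part of the choice nor named in the omics analyses, and the shown text does not fix the classifying visit. A difference in starting vision between the groups is likely, and markers of starting vision may be taken for response markers.

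The size rests on correlations that the article does not give. It ranges from nothing, if change is unrelated to baseline or the marker is, to a baseline gap of about one SD and false-positive rates above one half at the upper end. A reader might infer that the biomarkers will track starting vision; the documents support only that they may. The point is worth acting on because V1 BCVA is already collected and using it is cheap.

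**What to change.** 1. State one visit at which omics response is classified. V3 agrees with the 3-month item in *Secondary outcome*; use V5 as a sensitivity analysis.
2. Select the 250 and 250 within disease, matched on baseline-BCVA band and age band. For patients already picked, include baseline BCVA, age and disease as covariates in every omics response model.
3. In the whole-cohort validation, use the response definition in *Primary outcome* (gain of at least 5 letters) or continuous BCVA, in either case adjusted for baseline BCVA.

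**Cost.** This is a change to the selection and analysis wording. BCVA, demographic data and ocular history are recorded at V1 (Table 1), so no new measurement is needed. The contrast between the groups becomes slightly smaller after matching. *Participants and recruitment* reports 3055 patients recruited and the primary pharmacogenomic analysis under way, so samples already analysed can only be adjusted, not rematched.

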### Participants and recruitment

More than 5000 patients will be recruited from 43 ophthalmic centers in china that suffer from AMD, PCV, and PM (List of Ophthalmic Center in Additional file 3). And it is the first time for them to receive ocular injection of Conbercept. Doctors in outpatient clinic who diagnose and prescribe are independent of the investigators in this study. The 43 ophthalmic centers cover most regions of China. The recruitment capacity of each center will be mainly depended on the daily outpatient and registration capacity, as well as follow-up conditions. Participation is voluntary and consent is obtained before the procedures. Until now, the recruitment and primary pharmacogenomic analysis is ongoing and 3055 patients have been recruited.

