
### Data analysis

All data will undergo statistical tests, analysis will be based on baseline and follow-up data. In case of missing value, statistician will take out corresponding countermeasures in according to the provenance mechanisms of the missing data and the practical situation. Quantitative data will be described by “mean ± standard deviation” or “Median (Range)” and compared using Student’s t test, analysis of variance (ANOVA) and nonparametric test between two or multiple groups. Data for repeated measurements will be compared using multivariate analysis of variance (MANOVA) or trend test. Qualitative data is described by “Frequency (percentage)” and analyzed by the chi-square test (or Fisher’s exact test, if appropriate), and nonparametric test in differentiation among the groups. Pearson correlation or Spearman rank correlation will be used for correlation analysis. Multivariate statistical analysis including multiple linear regression, logistic regression, cox proportional hazards model, factor analysis, path analysis will be implemented in multivariate analysis or modeling process according to the data type. In case of multiple dimensional correcting issues of confounding factors, which can not be adjusted by multivariate model, then propensity score matching (PSM) or inverse probability weighting (IPW) will be applied. Such as Nomogram or classification and regression tree (CART) will be implemented to establish predictive models which could predict patients’ response to drugs (curative effects) in different diseases and proper subgroup analysis in clinically important indicators will be applied to find out high-benefit population. The models will be evaluated using the receiver operating characteristic-derived area under the curve (AUC) or Harrell concordance index (C-index), calibration plot, and decision-curve analyses (DCAs).

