Other anti-VEGF drugs such as ranibizumab or bevacizumab have been studied in treating PCV and CNV secondary to PM, and they had demonstrated effects on improving visual acuity and CRT [21–23]. However, the mechanisms of Conbercept in inhibiting VEGF function is different from the other anti-VEGF drugs, and whether the newly-developed drug is safe and efficacious for PCV and CNV secondary to PM have not been estimated. In our study, numerous clinical data we collected may provide convincing evidence for applications of Conbercept in PCV and CNV secondary to PMand may benefit further RCTs.

In the present study, we will use pharmacogenomics and pharmacometabolomics to investigate the biomarkers on the efficacy of Conbercept treatment. It has been reported that some patients have poor or no response to anti-VEGF drugs [24–26], and extensive and repeated administration of anti-VEGF drugs often leads to unnecessary wastes. Previously, researchers had found that gene polymorphism is associated with AMD patients’ response to intravitreal injection of anti-VEGF drugs and therapeutic regimen [27]. However, most of the studies analyzed assessed limited number of SNPs and their interactions with patients’ response to ranibizumab, the number of injections needed to maintain visual gains [27]. In this study, whole genome information may provide much more important data. Besides, there are no reported study involving pharmacometabolomics on Conbercept treating AMD, PCV, and CNV secondary to PM. In our study, we will select some patients for whole-genome sequencing and pharmacometabolomics analysis, then validate among larger populations. We expect to find new predictors of patients’ response to Conbercept, and the outcome would help doctors to treat these patients effectively, further develop individualized therapy, and improve patients’ compliance.

Although we will comprehensively investigate the clinical data, genome information, and metabolic factors of Chinese population, the current study still lacks clinical information in other human races. Therefore, further worldwide clinical studies are still needed to testify the above-mentioned results in other human races.

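### Response predictors are validated in a population that still contains the 500 patients in whom they were found, which roughly doubles to triples the rate at which noise markers pass

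*Protocol article*

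**What the plan says.** Under Study design and objectives, the article describes the discovery step: "We will pick up 500 patients, half of them have good response from significant effective group and half have no response from deterioration group". These patients' blood samples are analysed for response-associated predictors. The same sentence then fixes the validation set: "the predictors of patients’ response to Conbercept will be further validated in all of the recruited subjects".

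Secondary outcome repeats the choice twice. A sequencing panel is designed "to validate the Conbercept-sensitive genomic regions among the whole study population", and the associations of genotype and metabolites with the clinical endpoint are to be "further validated in the whole study population". The Discussion says only that the investigators will "then validate among larger populations", without saying whether those populations are separate from the discovery patients.

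On size, Participants and recruitment states: "More than 5000 patients will be recruited from 43 ophthalmic centers". Data analysis sets a p<0.05 cutoff for ranking predictors and names AUC or C-index, calibration plots and decision curves for model evaluation. It does not tie these measures to a particular data set.

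**The concern.** Validation asks whether a finding holds in data that had no part in producing it. Here the validation set contains the discovery set. A marker that looked good by chance in the 500 brings that chance association into the whole-cohort test. The overlap is aligned with the endpoint as well: every discovery patient with a gain of at least 15 letters is a responder under the 5-letter definition, and every one with a loss of at least 5 letters is a non-responder.

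The article says that signatures coming through this step will be treated as predictors of response, and the Discussion expects them to guide individualised therapy. A validated label resting partly on the discovery data would overstate the evidence for them.

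**Working it through.** The article gives no error rate or power figure for discovery or validation, so there is no stated result to reproduce. The size of the effect has to be computed under assumptions.

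**From the article.** Discovery set 250 + 250 = 500. Planned N above 5000 (5000 used here). 3055 recruited at the time of writing. Loss to follow-up to be kept below 20%, so possibly about 4000 evaluable. Cutoff p<0.05.

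**Assumed.** Two-sided tests; response rate 40–60%; letter change normal with mean/SD 9/15, 8/15, 5/12 or 9/13; random draws within each grade; independent null markers; the same visit used for grading and validation.

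**1. Overlap by headcount.** 500/5000 = 10%; 500/4000 = 12.5%; 500/3055 = 16.4%.

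**2. Single null marker, binary response.** The correlation between the discovery statistic and the whole-cohort statistic is ρ = √[(1/n_R + 1/n_N)/(2/250)], where n_R and n_N are the whole-cohort numbers of responders and non-responders.
- N=5000, 50% response: √[(2/2500)/(2/250)] = √0.100 = 0.316.
- N=5000, 60% response: √[(1/3000 + 1/2000)/0.008] = √0.104 = 0.323.

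Integrating the bivariate normal gives P(|Z_all|>1.96 given selection in the 500):

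| N | after p<0.05 | after p<0.001 |
|---|---|---|
| 5000 | 10.3–10.5% | 19–20% |
| 4000 | 11.6–11.9% | 23–24% |
| 3055 | 13.7–14.1% | 29–30% |
| patients outside the 500 | 5% | 5% |

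Counting only passes in the same direction, the N=5000 figure is about 10% against 2.5%.

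**3. Single null marker, continuous letter change.** Here ρ = √0.10 × (m_U + m_L)/2, where m_U and m_L are the mean distances of the two grades from the cohort mean, in SD units. For mean 9, SD 15: m_U = 1.069 and m_L = 1.472, so ρ = 0.316 × 1.27 = 0.402 and 13.6% pass. The other three distributions give 13.6–15.4%.

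**4. Simulation at N=5000.** Three of the distributions (8/15, 5/12, 9/13), with 40,000 null markers each, gave 9.4–11.2% for binary response and 14.5–15.0% for continuous change in all patients, against 4.8–5.8% outside the 500. A separate run at 9/15 with 60,000 markers gave 10.1% and 12.7%, against 4.5% for both.

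**5. Multi-marker models, if fitted in the 500 and scored in everyone.**
- Least-squares score on the top 50 of 2000 noise markers: mean AUC 0.89 in the 500, 0.544–0.547 in all 5000, and 0.500–0.502 outside the 500. With a null standard error of about 0.008, all replicates exceeded 0.5 + 1.96 SE in the full cohort, against 5% outside it.
- Minimum-norm linear classifier on 1000, 2000 and 5000 noise features: AUC 0.566, 0.592 and 0.597 in all 5000.
- Upper reference, a rule that memorises the 500: with f = 250/2500 = 0.10, AUC = f² + 2f(1−f) + (1−f)²/2 = 0.010 + 0.180 + 0.405 = 0.595.

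**6. What exclusion does to the remaining set (mean 9, SD 15).** The two grades hold about 1723 and 877 of 5000. Removing 250 from each leaves 627/4500 = 13.9% deteriorating, against 877/5000 = 17.5%. The overall response rate moves only from 60.5% to 61.7%. The 500 carry about 19% of the sum of squares of letter change. The standard error therefore rises by √(5000/4500) = 1.054 for binary response and by up to √(1/0.81) = 1.11 for continuous change.

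**The case against.** The strongest reply is that this is a condensed article. Full protocol version 2.0, the additional files, the flowchart and any analysis plan are not shown, and they may exclude the 500 or specify resampling. That disposes of any complaint that the article omits a hold-out or an optimism correction. It does not dispose of this point, because the article is not silent about the validation set: it names all recruited subjects once and the whole study population twice. A fuller document that excluded the 500 would contradict this text.

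Three stronger readings are tempting, and the documents do not support them.
- A reader might infer that noise markers will generally appear to validate. At N=5000 about 85–90% of those selected at p<0.05 would still fail.
- A reader might infer that the reported AUCs are bound to be inflated. The article does not say that the prediction model is fitted in the 500, and the AUC sentence in Data analysis names no data set, so the AUC figures are conditional. Only linear models were run; nothing was computed for random forests or support vector machines.
- A reader might take the 500 to be the very best and very worst responders. They are drawn from two grades defined by letter thresholds. True extremes would carry about 44% of the outcome variation, not 19%.

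It is also fair to say that predictor work is listed as a secondary outcome and worded as exploratory, and that the repair comes at the analysis stage with no data lost. Both points limit the severity.

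**Conclusion.** The point holds in a limited form. By its own stated rule, the article counts the discovery patients again as validation evidence. At the planned size, null markers selected at p<0.05 pass about two to three times as often as the nominal 5%: about 10% for binary response and about 13–15% for continuous change. The rate is higher with fewer evaluable patients or stricter selection. A noise model fitted in the 500 and scored in everyone would show an AUC of about 0.54–0.60 and would usually test as better than chance.

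The binary-response figures depend little on the response rate between 40% and 60%. The continuous-change figures rest on an assumed normal distribution of letter change, and the AUC figures also rest on a workflow the article does not state. The consequence is confined to the secondary predictor aim.

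**What to change.** In Study design and objectives, and at both places in Secondary outcome, replace the whole-cohort wording with: all recruited subjects outside the 500 discovery patients. Add that the marker list, and any model and cutoff derived in the 500, are locked before validation data are analysed. Estimates that include all patients may still be reported, labelled as descriptive and not as validation.

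The remaining roughly 4500 are outcome-selected, so calibration and decision curves there should either carry weights for the known selection or state the caveat. Under the assumed distribution (mean 9, SD 15) the weights would be 877/627 = 1.40 for the deterioration grade, 1723/1473 = 1.17 for the significantly effective grade and 1 otherwise. They are valid if the draw within each grade is random, so the method of drawing should be stated too.

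The cost is a short text change, a dataset flag and the weighting step. Standard errors rise by about 5% for binary response and up to about 11% for continuous change. No new patients or samples are needed.
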